### Outcome measures

#### Primary outcome

The primary outcome is reduction from baseline of the mean number of medium term (4–9 days) sickness absences from the workplace per intervention and control centre after 1 year of follow-up as measured by OHS patient records. We chose medium-length sickness absences as the primary outcome to ensure that we have a sufficient number of cases to assess impact. Within the Pihlajalinna Työterveys cohort in 2015, there were 17,794 instances of sickness absences between 4 and 9 days in duration. This outcome is also supported by a large Finnish study on over 6000 municipal workers [26] which indicated that sickness absences of between 4 and 9 days were more prevalent (85.7 and 59.0 per 100 person-years for women and men, respectively) than those over 2 weeks (10+ days) in duration. The study also indicated that self-certified (1–3 days) absences were the most common (156.4 and 96.1 per 100 person-years for women and men, respectively), but these are not reliably available from the electronic patient register held by Pihlajalinna Työterveys. Longer sickness absences (between 2 weeks and 60 days) are less prevalent and had rates of 22.8 and 18.0 per 100 person-years for women and men, respectively, with long absences of over 60 days being relatively infrequent (4.7 and 4.4 per 100 person-years for women and men, respectively) [26]. Shorter (1–3 days) sickness absences were not included as a primary outcome, because they are not reliably available from the patient register, and they have been found not to be associated with disability pensions, except through their association with longer-term (3+ days) sickness absences [9]. Long (3+ days) sickness absence spells have been found to be predictive of work disability before the age of 55 [9] and regardless of health status [27].

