### Power calculation

The pre-study power and sample size calculations for our main outcome were based on data collected in 2015 with estimates of the individuals between the ages of 18 and 65 from the 22 OH units (*n* = 24,892). The 22 clusters had an average size of 2300 individuals. We estimated the intra-cluster correlation coefficient to be 0.05. We used the n4means function in the CRTSize package in R [28], which takes into account that the outcome for individuals cannot be assumed to be independent. We used a two-sided alpha of 5% for our primary outcome, the sickness absences of medium (4–9) days, with an SD of 1.5. With 11 clusters randomised to each arm (assuming 2300 individuals per OHS), the study had 91% power to detect at least a 10% difference between individuals in the intervention and control OHS groups. These calculations showed that even with a 20% loss to follow-up or missing data, we would still have 90% power for the primary analysis.

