## Discussion

The wealth of registers, especially in Nordic countries, allows for innovative research to be conducted with minimal need for additional data collection or trouble for the participants. Recent authors have argued that registry trials can have a wealth of benefits, but quality issues need to be taken into account [29]. Our pragmatic trial uses the combination of electronic health records with registries and tests a real-world intervention with a good study design and maximum external validity [30] with little disruption to the physicians implementing the study [31]. The trial is pragmatic in nature, and thus, while yielding results highly transferable to other settings, there are statistical challenges in design. These include, for example, the high variation in cluster size, which may reduce the power. Regardless of this, we expect the cluster and total sample sizes to be sufficient to detect a true difference, and the impact of the cluster size variation can be determined during analysis.

While interesting from a methodological standpoint, the practical impact of quality improvement in occupational health care has implications beyond this trial and this particular consortium. Through assessment of work-relatedness of each visit, primary care visits can be used effectively as a tool for secondary prevention and early intervention. These approaches can be used also in settings where occupational health care is not statutory. Studies have indicated that the recording of work-relatedness of visits is not optimal [32], and approaches such as this built into services could potentially improve reporting. Improved reporting and recognition can also contribute to collaboration between OHS and employers and general practitioners [33]. These issues are important particularly in Europe, where the population is ageing and life expectancy is increasing and where economic development depends on a healthy workforce.

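### The stated 91% power for a 10% difference does not hold for the number of 4–9 day absence spells: the stated inputs give about 8%, and 91% needs a mean near 5

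*Protocol article*

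**What the plan says.** In the protocol article, Outcome measures defines a count: "The primary outcome is reduction from baseline of the mean number of medium term" (4–9 day) absences per centre, after one year. The same section reports that in the provider's 2015 cohort "there were 17,794 instances of sickness absences between 4 and 9 days in duration".

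Power calculation addresses that outcome: "We used a two-sided alpha of 5% for our primary outcome", "with an SD of 1.5". It adds "We estimated the intra-cluster correlation coefficient to be 0.05" and "The 22 clusters had an average size of 2300 individuals", while giving n = 24,892 for the 2015 planning data. With 11 units per arm it concludes that "the study had 91% power to detect at least a 10% difference between individuals in the intervention and control OHS groups", and that 90% remains after 20% loss or missing data. It states neither the control mean, nor the unit of the SD, nor the absolute difference behind the 10%.

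The Discussion concedes that variation in unit size may lower power, then says: "Regardless of this, we expect the cluster and total sample sizes to be sufficient to detect a true difference".

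**The concern.** A 10% relative difference becomes a power only through a mean, and none is given. With 22 clusters and an ICC of 0.05, the between-unit variance sets the precision, however many employees each unit has. An SD of 1.5 then leaves little chance of detecting 10% of a count whose mean is below 1.

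If the stated power is wrong, a null result would be read as evidence against a 10% reduction when the trial could not have detected one. According to Trial status the trial has ended, so the consequence lies in how its result is interpreted.

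**Working it through.** **Inputs**
- From Power calculation: k = 11 units per arm, m = 2300 per unit, ICC = 0.05, SD = 1.5, two-sided alpha 0.05.
- Mean number of spells (derived): 17,794 (Primary outcome) / 24,892 (Power calculation) = 0.715 per person.
- Other bases in the protocol: 17,794/67,000 listed employees (Setting) = 0.266; 17,794/(22 × 2300) = 17,794/50,600 = 0.352; the cited municipal-worker rates of 0.857 (women) and 0.590 (men) per person-year.

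**Standard error**
- Design effect = 1 + (m − 1) × ICC = 1 + 2299 × 0.05 = 115.95.
- Effective n per arm = 11 × 2300/115.95 = 218.
- SE = SD × √(2 × design effect/(k × m)) = 1.5 × √(2 × 115.95/25,300) = 0.1436.

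**Reproducing the 91%** (noncentral t, 2 × (11 − 1) = 20 df)
- The difference needed is 0.499; the normal approximation gives (1.960 + 1.341) × 0.1436 = 0.474.
- A difference of 0.50 gives 91.2%. With 20% fewer individuals (m = 1840) it gives 91.1%, in line with the protocol's claim of 90% after loss.
- So both stated powers come out for a difference of 0.50, which is 10% of a mean of 5.

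**Power for 10% of the number of spells**

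| Mean spells per person | 10% difference | Power |
|---|---|---|
| 0.715 | 0.0715 | 7.6% |
| 0.857 | 0.0857 | 8.8% |
| 0.590 | 0.0590 | 6.8% |
| 0.352 | 0.0352 | 5.6% |
| 0.266 | 0.0266 | 5.4% |

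At a mean of 0.715 the normal approximation gives 7.9%.

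**Detectable difference**
- With 91% power: 0.499 spells, and 0.499/0.715 = 70% of the mean.
- With 80% power: 0.423 spells, or 59%.

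**Other readings of the 10%**
- Absolute difference of 0.10: 10%.
- Difference of 0.1 SD = 0.15: 17%.
- 10% of all spells (72,000/25,000 = 2.88 per client, Assessment points; difference 0.288): 48%.
- m = 1131 in place of 2300: 7.6% at a difference of 0.0715, unchanged.

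**What would restore 91% at 0.0715**
- An ICC of about 0.0006; or
- at ICC 0.05, an SD of about 0.2, although a pure Poisson count with mean 0.715 already has SD √0.715 = 0.85; or
- adjustment for the unit's baseline rate with a very high unit-level correlation r. Scaling the SE by √(1 − r²), r = 0.9 gives 0.1436 × √0.19 = 0.0626 and 19% power; r = 0.99 gives 92%.

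**Secondary checks**
- Sample size: 24,892/22 = 1131, not 2300, and 22 × 2300 = 50,600. The figures disagree, but at this ICC the effect on power is negligible (90.9% against 91.2% for a difference of 0.50).
- Unequal sizes: Participants and recruitment gives units of 500 to 9000 employees. With design effect 1 + ((1 + CV²)m − 1) × ICC and an assumed size CV of 0.6, 0.8 or 1.0, the design effect is 157, 190 or 231. A size-weighted analysis then has 81%, 74% or 65% power, even for a difference of 0.50.
- Loss of two whole units per arm (k = 9): 84% for a difference of 0.50.

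**The case against.** The strongest reply is that 8% is not the trial's true power either. Power calculation gives no mean. The 0.715 joins a spell count from one section to a headcount from another, and the article does not say that they cover the same people. The ICC of 0.05 is an estimate with no basis shown. With SD 1.5 it implies a between-unit SD of 1.5 × √0.05 = 0.335, about 47% of the mean. At a smaller ICC power rises: 18% at 0.01 and 80% at 0.001. The outcome is a change from baseline, which may remove some between-unit variance. All of this stands, and it makes 8% a conditional figure. It does not rescue the 91%, which was itself calculated at ICC 0.05 and SD 1.5.

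It is also fair that a mean of 5 as the length in days of a 4–9 day spell is an inference. It would fit the SD of 1.5, but the article does not say so, and the inconsistency does not depend on it.

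Three further points stand in part. The 90% sentence follows from the protocol's own calculation and falls only with the 91%; loss of whole units is a scenario that it does not claim to cover. The Discussion already discloses the unequal unit sizes. And the planned rate ratios with 95% confidence intervals would show the imprecision of a null result, though they would not correct the stated power.

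**Conclusion.** The power statement is wrong as written. With the stated SD, ICC and cluster numbers, 91% holds for a difference of about 0.50, and the article gives no mean number of 4–9 day spells near 5. For a 10% difference in the defined primary outcome, the same inputs give about 8% (5–9% over the bases that the protocol offers), and the difference detectable with 91% power is about 70% of the mean. This rests on SD 1.5 and ICC 0.05 as stated, on the derived mean of 0.715, and on no gain from baseline adjustment, for which no correlation is given. The true power may be higher than 8%, but these inputs do not support 91%. The mismatch between n and mean cluster size is real but minor. The unequal-size and whole-unit-loss figures are illustrations.

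**What to change.** - Recompute the power for the number (rate) of 4–9 day spells. State the baseline mean rate, the between-unit variation estimated from the 2015 unit data, the actual unit sizes and 20 degrees of freedom.
- Include the gain from adjusting for each unit's baseline rate, and state the correlation used.
- Replace the claim of 91% for 10% with the resulting power or detectable rate ratio. Give the absolute difference and the unit of the SD.
- Restate or remove the dependent 90% sentence. If loss is to be covered, express it as loss of units.
- Use one sample size and one mean cluster size, and say which population each describes.
- Bring the Discussion's statement on sufficient sample size into line.

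The cost is a recalculation from data already held and corrected text. Recruitment, design and analysis do not change. The reported power is likely to be much less favourable.

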### Data collection

Data on patient visits to the OHS unit were collected from a central patient register. Self-reported sickness absences of between 1-3 days are reported by the employer to the OHS unit. Pre-intervention data were extracted by the information technology service provider of Pihlajalinna Työterveys, who provided coded and anonymised patient data, a separate list of personal identifiers and a code for combining the patient data with the personal identifier. The list of personal identifiers was sent to the Finnish Centre for Pensions, which holds a registry of pensions, including disability pensions, for the entire population. The Finnish Centre for Pensions extracted data on pensions for the entire list of personal identifiers and coded it with the same code. The pseudonymised patient data and coded pension data were sent to the University of Tampere. The same process will be repeated for data collected during and after the intervention.

### Data management

The data from the Finnish Centre for Pensions and Pihlajalinna Työterveys were combined on the basis of patient codes at the University of Tampere using R software. Data were kept on a secure server, password-accessible only to the research team. Data accuracy will be checked by referring back to the OHS units for details where there are suspected errors in data entry. The Finnish Centre for Pensions register system checks the data automatically, and the data are routinely reviewed and corrected.

### Data analysis

Data will be analysed on the intention-to-treat principle. All employees registered at a cluster will be analysed as part of that cluster. We will use both R and IBM SPSS Statistics software (IBM, Armonk, NY, USA) to analyse the data. We will first examine the data using descriptive statistics. Between-group analysis will be conducted using Pearson’s chi-square test or Fisher’s exact test for categorical data and Student’s *t* test or the Mann-Whitney *U* test for continuous variables, depending on normality of a distribution. The normality of the distribution of the variable will be examined with the Kolmogorov-Smirnov test. The intervention effects for primary and secondary outcomes will be analysed using regression analysis, logistic regression will be used for dichotomous outcome variables, and Poisson regression will be used when the outcome variable is a count. In both analyses, we will examine the impact of, and control for, possible confounders. The regression analysis will result in ORs and rate ratios with 95% CIs. The results will be considered significant at *p* < 0.05. For analysing the differences in duration of sickness absences, we will use Kaplan-Meyer survival curves and the log-rank test.

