**Methods/design:**

A pragmatic trial will be conducted using patient electronic registers and registers of the central pensions agency in Finland. Twenty-two occupational health centres will be randomised to intervention and control groups. Intervention units will receive training to improve recording of work ability illnesses in the primary care setting and improved follow-up procedures. The intervention impact will be assessed through examining rates of sickness absence across intervention and control clinics as well as before and after the intervention.

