### Randomisation and allocation

To allocate OH units into intervention and control groups, a randomisation process using dynamic allocation (specifically minimisation) was used. This method was first presented by Taves [22] and later by Pocock and Simon [23]. The use of minimisation has increased in recent years [24], and it has been suggested as the ‘platinum standard’ of trials [25] because it allows for balance between treatment and control arms. In this trial, we considered the following as potential confounders and included them in the minimisation: (1) the client volume of the OHS separated into three enterprises—small, medium and large, (2) the main sector of the OHS clients (industry vs others) and (3) whether one of the OHS unit’s enterprise clients was a major paper factory or not (the paper factory had instituted large-scale OH interventions in recent years).

We began the randomisation with simple randomisation conducted by the team statistician (NT). We allocated the first four units through simple randomisation (1:1) using the random number generator in the R program (R Foundation for Statistical Computing, Vienna, Austria). For the remaining 18 units, we used minimisation to allocate each OHS unit to either the treatment group or the control group to minimise the total imbalance for potential confounders, continuing with a 1:1 ratio. Because the intervention was embedded in routine practice, allocation was concealed from participants but not from providers or investigators. The concern of lack of blinding during the minimisation process did not apply in this case, owing to the cluster-based design and the fact that both the intervention and control clusters are part of Pihlajalinna Työterveys.

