### Assessment points

Baseline information will be assessed for 1 year preceding the intervention, from 1 May 2015 to 1 May 2016. Approximately 72,000 spells of sickness absence were registered among 25,000 clients at Pihlajalinna Työterveys in 2015. For the primary outcome (mean sickness absence of medium length after the intervention compared with baseline), assessment will be conducted by NT after 1 year of the intervention, using data up to 1 May 2017 (*see* Fig. 1 for trial flow and Fig. 2 for SPIRIT diagram). For mean disability pensions per centre, the time will be increased to 31 December 2017, with subsequent analysis hoped for after more funding is received.

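### The primary outcome is a change from baseline, but the only models named are for counts and yes/no outcomes, with no stated role for baseline or the minimisation factors

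*Protocol article*

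**What the plan says.** The Primary outcome section of the Protocol article defines the outcome as "reduction from baseline of the mean number of medium term (4–9 days) sickness absences from the workplace per intervention and control centre" after one year. The Assessment points section repeats the idea, "mean sickness absence of medium length after the intervention compared with baseline", and says that a full baseline year is held: "Baseline information will be assessed for 1 year preceding the intervention".

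The Data analysis section sends intervention effects for primary and secondary outcomes to regression and then names two kinds: "logistic regression will be used for dichotomous outcome variables, and Poisson regression will be used when the outcome variable is a count". The output is fixed too: "The regression analysis will result in ORs and rate ratios with 95% CIs". Covariates get one sentence: "In both analyses, we will examine the impact of, and control for, possible confounders". Baseline is not mentioned in that section.

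The Randomisation and allocation section does name covariates: "we considered the following as potential confounders and included them in the minimisation". They are client volume in three classes, main client sector, and whether a major paper factory is a client. The Data analysis section does not refer back to them.

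**The concern.** A reduction in a mean is neither a count nor a dichotomy. Neither named model estimates it as defined, and neither an odds ratio nor a rate ratio expresses it. An analyst following the text must choose among a follow-up-only comparison, a change score and a baseline-adjusted comparison. These differ in precision, and with 22 units precision is scarce.

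The covariates raise a smaller point. Balance was forced on three factors, and an analysis that leaves them out does not reflect how the units were allocated. All the variables needed are already held, so nothing practical prevents the analysis from being fixed in the text.

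**Working it through.** **1. Outcome and model side by side.** The outcome is the follow-up mean set against the baseline mean, per centre, on a continuous scale with either sign. The models are logistic for dichotomies and Poisson for counts, giving odds ratios and rate ratios. The same section lists a t test and a Mann-Whitney test for continuous variables in between-group comparisons, but it assigns intervention effects to regression. A Poisson model of absence counts with a baseline term, or with two periods, could answer the question. The text does not state one.

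**2. Inputs.** The Power calculation section gives an intra-cluster correlation of 0.05, 2300 people per unit, 11 units per arm, SD 1.5 and two-sided alpha 5%. The Participants and recruitment section gives units of 500 to 9000 employees. The between-year correlation of unit rates is not given, so 0.8, 0.5 and 0.3 are assumed.

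**3. Reliability of a unit mean.** This is m × ICC / (1 + (m − 1) × ICC).
- m = 2300: 115 / 115.95 = 0.992.
- m = 500: 25 / 25.95 = 0.963.

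At this ICC almost all variance of a unit mean lies between units, even in the smallest unit. How much of it persists from one year to the next is a separate matter, on which the ICC says nothing.

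**4. Variance relative to a follow-up-only comparison.** Let r be the observed correlation, that is, the assumed true correlation × 0.992. A change score has factor 2(1 − r). Baseline adjustment has factor 1 − r².

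| True correlation | r | Adjusted, 1 − r² | Change score, 2(1 − r) |
|---|---|---|---|
| 0.8 | 0.793 | 0.370 | 0.413 |
| 0.5 | 0.496 | 0.754 | 1.008 |
| 0.3 | 0.298 | 0.911 | 1.405 |

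Since 1 − r² = (1 − r)(1 + r) and 1 + r is at most 2, the adjusted variance never exceeds that of the change score. It never exceeds 1 either. The change score is worse than ignoring baseline once r falls below 0.5.

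**5. Degrees of freedom.** There are 22 − 2 = 20 at unit level. Baseline takes 1 and the minimisation factors take 2 + 1 + 1 = 4, which leaves 15.

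**6. What this means for power.** The plan gives no figure for this point; the nearest is its 91% power. With its SD, ICC and cluster size, the normal formula needs a difference of (1.960 + 1.341) × 1.5 × √(2 × 115.95 / 25,300) = 0.474 to reach 91%. Whether 0.474 matches the plan's 10% is a separate matter; here it serves only as a reference difference. A follow-up-only t test on 20 df then has 88% power.

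| Observed r | Change score | Baseline-adjusted, 19 df | Plus minimisation factors, 15 df |
|---|---|---|---|
| 0.3 | 76% | 91% | 90% |
| 0.5 | 88% | 95% | 94% |
| 0.7 | 98% | 99% | 99% |

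The last column gives no credit for variance that the factors explain.

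**7. Leaving out the minimisation factors.** Minimisation of 22 units was simulated, with 4000 runs per setting. The factors were assumed to explain 0, 30% or 60% of the residual unit variance. Without the factors, the baseline-adjusted test had type I error of about 5%, 2% and 0.6%. With them it stayed between 4.4% and 5.3%.

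**The case against.** The strongest reply is that a condensed article commonly leaves covariate lists and the baseline term to an analysis plan that is not shown. The possible confounders of the Data analysis section may also simply be the three potential confounders already named under Randomisation and allocation. Both points are fair. The missing covariate list alone would not be a finding, and the covariate part is the weaker one. The reply does not remove the mismatch between outcome and model, because both sides of it are in the article. It is also right that Poisson is not assigned to the primary outcome by name.

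A reader might infer more than the document supports:

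- **Covariates chosen after seeing results by arm.** The sentence speaks of examining impact and controlling. It does not say that covariates are kept or dropped on that basis. The same team statistician allocates units and assesses the outcome, but that does not show such a choice.
- **An uncontrolled before-after test.** The abstract speaks of "examining rates of sickness absence across intervention and control clinics as well as before and after the intervention". This fits a comparison of changes between arms at least as well. The falling trend in the Background concerns disability pensions, and a concurrent control arm handles a trend common to both arms.
- **False positives from omitting the minimisation factors.** Step 7 shows the opposite direction.
- **A large gain from baseline adjustment.** At a correlation of 0.3, 91% of the variance remains.

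**Conclusion.** The concern holds as a mismatch inside the article. The primary outcome is a per-centre change from baseline; the named models and effect measures do not estimate it, and the role of baseline is not stated. The lack of a commitment to the minimisation factors is secondary.

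The size depends on the assumed correlations and on equal units at the plan's ICC. Read literally as a change score, the outcome has a variance between 41% and 140% of the follow-up-only variance over the range examined. Baseline adjustment lies between 37% and 91% and is never the worse of the two. The cost of leaving out the minimisation factors is lost precision and a conservative test, by an amount that depends on how much variance they explain. This is a worthwhile and cheap correction; it is not evidence that the planned analysis would be biased.

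**What to change.** State one primary analysis, and word the outcome to match it. Compare the follow-up rate of 4–9 day absences by arm, in a model that respects clustering by unit. Adjust for the unit's log baseline rate, client volume (three levels), sector and paper-factory client, and report a rate ratio with its 95% CI. A unit-level baseline rate suits the open cohort, since people who join later have no individual baseline.

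If a two-period model is preferred, constrain the arms to a common baseline mean. With free baseline means, the arm-by-period term is the difference in changes and carries the change score's variance.

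Label other adjusted analyses and within-arm before-after contrasts as descriptive. The Trial status section says that the trial ended on 1 May 2017, so the wording should be fixed and dated before outcomes are examined by arm.

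The cost is wording plus about 5 of 20 unit-level degrees of freedom. The 4 spent on the minimisation factors take about 1 point of power or less in the cases above. No new data are needed.
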